### Planned interim analysis

The first after 144 patients and the second after 386 patients were treated. The expected local recurrence rate is 0.5/1/1.5% after 2.5/5/7.5 years, respectively. Stopping rules for the study are if the local recurrence rate is higher than 3/4/6% after 2.5/5/7.5 years. Therefore the efficacy of IORT will be rejected if more than 5 or > 8 patients show a local relapse, respectively.

An interim analysis of late breast toxicity is planned after a two-year follow-up of the first 144 patients. Results will be presented as frequency tables.

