### Recruiting

first patient: January 2011

last patient: December 2015

follow-up: 10 years

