## Statistical calculations for trial sample size

### Study hypothesis

This study is designed to confirm the non-inferiority of IORT in comparison to WBRT in elderly patients with low risk breast carcinoma.

Power calculations with an alpha set at 0.01, a beta set at 0.05 (power 95%), and an anticipated drop-out rate of 20% and a loss to follow-up of 20% result in 540 patients to be included. Calculations of the sample size were performed as described by A’Hern
[8], Simon
[9] and Fleming
[10]. Each stratum has to recruit at least 270 patients.

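### The two efficacy analyses are triggered by patients treated, with no minimum follow-up, although the rejection counts are five-year boundaries, so the rule as written lacks the stated 95% power

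*Protocol article*

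**What the plan says.** Under *Planned interim analysis*, the protocol article sets the timing of the two efficacy analyses: "The first after 144 patients and the second after 386 patients were treated". The same paragraph gives the anticipated rates ("The expected local recurrence rate is 0.5/1/1.5% after 2.5/5/7.5 years, respectively"), the unacceptable rates ("Stopping rules for the study are if the local recurrence rate is higher than 3/4/6% after 2.5/5/7.5 years") and the decision rule: "the efficacy of IORT will be rejected if more than 5 or > 8 patients show a local relapse, respectively". Nothing there says which of the three time points either count belongs to, or how long patients must have been followed.

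The next paragraph does attach follow-up, but only to toxicity: "An interim analysis of late breast toxicity is planned after a two-year follow-up of the first 144 patients".

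The list of stopping criteria under *Investigator withdrawal* repeats the criterion of more than 5 local relapses, tied only to the first safety report. *Study hypothesis* states alpha 0.01 and power 95%, cites A'Hern, Simon and Fleming for the method, and says that "an anticipated drop-out rate of 20% and a loss to follow-up of 20% result in 540 patients to be included". *Recruiting* gives a first patient in January 2011 and "last patient: December 2015".

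**The concern.** The rates at issue are defined at 2.5, 5 and 7.5 years, but the analyses fire on a head count that can be reached long before patients have been followed that far. A fixed relapse count has its designed error rates only if each patient's status is known at the time point used to derive it. Applied earlier, the same count is harder to reach, and the chance of stopping at an unacceptable rate falls.

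This is the quantitative efficacy rule of a single-arm trial in which whole breast radiotherapy is given only when risk factors are present. If the rule is followed literally, the first look has almost no chance of rejecting and the second has far less than the planned power.

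**Working it through.** **1. Reproducing the plan's counts.** Fleming's two-stage upper boundary at stage g is r_g = int[n_g·p0 + z·√(N·p0(1−p0))] + 1. Inputs are n_1 = 144 and N = 386 (*Planned interim analysis*) and alpha 0.01 (*Study hypothesis*). The sidedness is not stated; I take it as one-sided, so z = 2.326.

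| p0 (expected rate) | n_1·p0 + z·√(…) | N·p0 + z·√(…) | Reject at |
|---|---|---|---|
| 0.5% (2.5 y) | 3.94 | 5.15 | 4 and 6 |
| 1% (5 y) | 5.99 | 8.41 | 6 and 9 |
| 1.5% (7.5 y) | 7.72 | 11.35 | 8 and 12 |

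For p0 = 1%, z·√(386 × 0.01 × 0.99) = 4.55; 1.44 + 4.55 = 5.99 and 3.86 + 4.55 = 8.41. Rejecting at 6 and 9 is the same as rejecting at more than 5 and more than 8. Only the five-year rate gives the published counts.

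The total also reproduces: 386 × (1 + 0.20 + 0.20) = 540.4, so 540. The figure 386 therefore behaves as an evaluable sample size.

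With complete five-year status, the exact binomial P(>8 of 386) is 0.973 at 4% and 0.017 at 1%. The planned 95% power is met on that basis.

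**2. When the looks fall as written.** Accrual from January 2011 to December 2015 is 60 months. Assuming it is even, 540/60 = 9 patients per month.

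- First look: 144/9 = month 16. Mean follow-up is 0.67 years and nobody has reached 2.5 years.
- Second look: 386/9 = month 43. Mean follow-up is 1.8 years; 116 of 386 (30%) have reached 2.5 years and none 5 years.

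**3. Expected relapses and probability of stopping.** For patient i with follow-up f_i, p_i = 1 − exp(−h·f_i). Expected relapses are Σp_i, and the tail is that of a sum of independent Bernoulli(p_i) variables. The hazard is h = −ln(1 − rate)/time: 0.01218 per year from 3% at 2.5 y, 0.00816 from 4% at 5 y and 0.00825 from 6% at 7.5 y. Dropout is not modelled.

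| True rate | Look 1: expected | P(>5) as written | P(>5), complete status | Look 2: expected | P(>8) as written | P(>8), complete status |
|---|---|---|---|---|---|---|
| 3% at 2.5 y | 1.16 | 0.0012 | 0.26 | 8.28 | 0.45 | 0.82 |
| 4% at 5 y | 0.78 | 0.0001 | 0.52 | 5.58 | 0.11 | 0.97 |
| 6% at 7.5 y | 0.79 | 0.0002 | 0.87 | 5.64 | 0.12 | >0.99 |

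The complete-status columns assume that every patient's status is known at the time point in that row.

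**4. The protocol's own curve.** The unacceptable rates are front-loaded: 3% by 2.5 years and 4% by 5 years. With h = 0.01218 up to 2.5 years and −ln(0.96/0.97)/2.5 = 0.00415 after that, the second look expects 7.8 relapses and P(>8) = 0.38. The first look is unchanged from the 3% row, because nobody has passed 2.5 years.

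**5. Sensitivity to accrual.** With a slow start (cumulative accrual proportional to t^1.5 or t^2), the first look expects 1.0 to 1.5 relapses and stops with probability of at most 0.004. The second expects 4.4 to 7.4 and stops with probability 0.03 to 0.32.

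**The case against.** The strongest reply is that the published counts are themselves evidence of intent. They equal five-year boundaries and 386 inflates to 540, so 144 and 386 look like evaluable numbers with known status, and the trigger may be loose wording in a condensed article. That is plausible and the text does not rule it out. It does not remove the problem: the trigger is stated alongside its counts, a follow-up condition is attached to toxicity and not to efficacy, and a team following the words would look too early. It does mean that clarifying the trigger may be enough.

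Three stronger readings are tempting, and the document does not support them.

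- A reader might infer that almost no relapses could have occurred at either look. That fits the first. At the second, 5.6 to 8.3 would be expected at unacceptable rates, close to the cut of 8; the data are too early but not empty.
- A reader might take the 11% and conclude that about 89% of ineffective treatments would pass. That is one end of a range, and it is a probability under one assumed hazard, not a share of treatments. The chance of not stopping at the second look is about 55% to 89%, or 62% on the protocol's own curve.
- A reader might infer that getting past the second look declares the treatment effective. The article states only when efficacy is rejected. It also plans a 95% confidence interval for the relapse-free proportion, Kaplan-Meier plots and 10 years of follow-up, and lets the steering committee close the study early.

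**Conclusion.** The concern holds. The efficacy trigger carries no minimum follow-up and does not match the five-year basis of its own counts. Followed as written, the first look would stop an unacceptable treatment with probability of about 0.1% or less. The second would do so with probability of about 11% to 45%, against 97% for a 4% rate with complete five-year status. The stated 95% power is not delivered.

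The exact figures rest on even accrual, constant hazard and no dropout, none of which the document gives. The conclusion does not depend on even accrual: slow-start accrual lowers the second-look figures and leaves the first at 0.4% or less. Dropout would lower all of them. That the counts have a five-year basis is inferred from their exact match to the Fleming boundary, since the article does not state it.

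**What to change.** Under *Planned interim analysis*, and in the matching criterion of more than 5 relapses under *Investigator withdrawal*, tie each count to the follow-up it was derived for. Apply more than 5 of 144 and more than 8 of 386 when those evaluable patients have known five-year status, and label the second as the final efficacy analysis.

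Do not use these counts at any earlier look. Moving the first look to 2.5 years and keeping more than 5 of 144 would stop a 3% rate only 26% of the time. For a 2.5-year or calendar look, compare observed relapses with a boundary derived for that time point or for the person-years accrued.

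The wording change is small, but there is a cost in time. Under even accrual, if all treated patients are evaluable, the five-year looks fall at month 16 + 60 = 76 and month 43 + 60 = 103. With the planned losses they come later. Reaching 386 evaluable patients may need all 540, which puts the second look at up to about month 60 + 60 = 120. Both looks come after accrual closes at month 60, so an early person-years check is needed if the rule is to protect patients during accrual. It would add one small table.

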### Description of the primary efficacy analysis and population

A single group of patients is studied. The proportion of patients who respond to treatment (i.e. local relapse free) will be used to estimate the true response rate with a 95% confidence interval. A response rate of 99.5%/99%/98.5% at 2.5/5/7.5 years is anticipated. A response rate of 97%/96%/94% is considered to be the minimum level.

Therefore, efficacy analyses will be performed at two stages.

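### The last count-based efficacy limit (>8 relapses) is fixed at 386 patients treated, labelled interim, and does not hold the stated alpha of 0.01 at 5 years for 386 or for the number the plan's own losses would leave

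*Protocol article*

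**What the plan says.** In the protocol article, the section Study hypothesis sets alpha at 0.01 and beta at 0.05, and states that "an anticipated drop-out rate of 20% and a loss to follow-up of 20% result in 540 patients to be included". The section on the primary efficacy analysis gives the two rates to be told apart: "A response rate of 99.5%/99%/98.5% at 2.5/5/7.5 years is anticipated" and "A response rate of 97%/96%/94% is considered to be the minimum level". It continues: "Therefore, efficacy analyses will be performed at two stages".

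The section Planned interim analysis places those stages: "The first after 144 patients and the second after 386 patients were treated". Efficacy is rejected if more than 5 or more than 8 patients, respectively, have a local relapse. The same section has a rate-based stopping rule (above 3/4/6% at 2.5/5/7.5 years). The primary analysis is an estimate of the relapse-free proportion with a 95% confidence interval. No count limit is given for 540 or for any evaluable number other than 144 and 386, and neither count limit is tied to one of the three time points.

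**The concern.** The last numerical accept-or-reject rule belongs to a fixed number of treated patients, under a heading that implies a later, final decision. No such decision rule follows. A relapse limit has known error rates only for the denominator for which it was derived. If the number with known status at the deciding time point is not 386, a fixed limit of 8 has other error rates. With fewer evaluable patients it becomes too lenient, and a treatment at the minimum level is accepted more often than the plan allows. In a single-arm trial meant to confirm efficacy, this is the error that the alpha of 0.01 is there to control.

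**Working it through.** **Inputs.** Alpha 0.01, beta 0.05, losses 20% + 20%, N = 540 (Study hypothesis); relapse rates at 5 years p0 = 4% and p1 = 1% (primary efficacy analysis); limits 5 of 144 and 8 of 386 (Planned interim analysis). Assumed: one-sided alpha, the 5-year pair as the deciding one, and known 5-year status for every patient counted.

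**The plan's 540.** 386 x (1 + 0.20 + 0.20) = 540.4, so 540 is reproduced if 386 is the required evaluable number. The origin is inferred: 432 / 0.8 = 540 fits as well.

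**What 540 yields.** With 20% + 20% added, 540 x 0.60 = 324. With the two losses in sequence, 540 x 0.80 x 0.80 = 345.6, about 346. To retain 386, enrolment would have to be 386 / 0.64 = 603 or 386 / 0.60 = 643.

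**Acceptance probability with the look at 144 included.** For final number n and limit c:

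A(p) = sum over x = 0 to 5 of P[Bin(144, p) = x] x P[Bin(n - 144, p) <= c - x].

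A(4%) is the wrong-acceptance probability and A(1%) is the power.

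The printed limit of 8:

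| n | A(4%) | A(1%) |
|---|---|---|
| 386 | 2.68% | 98.1% |
| 346 | 6.1% | 98.9% |
| 324 | 9.2% | 99.2% |

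At 386 no limit meets both targets: 6 gives 0.51% and 90.4%; 7 gives 1.25% and 95.7%.

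The largest limit with A(4%) <= 0.01:

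| Evaluable n | Limit c | A(4%) | A(1%) |
|---|---|---|---|
| 324 | 5 | 0.99% | 89.1% |
| 346 | 5 | 0.55% | 86.4% |
| 386 | 6 | 0.51% | 90.4% |
| 432 | 8 | 0.95% | 96.7% |
| 540 | 11 | 0.81% | 98.8% |

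Under this rule both targets are met at every n from 430 to 540. Between 386 and 429 they are met only at 396 to 398.

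**With 386 kept as a look that can only reject (>8), and a final limit of 11 of 540.** Sum over x <= 5 and x + y <= 8 of P[Bin(144, p) = x] x P[Bin(242, p) = y] x P[Bin(154, p) <= 11 - x - y]. Result: 0.63% at 4% and 97.8% at 1%.

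**Dependence on the landmark.** The printed rule (5 of 144, 8 of 386) gives 17.7% wrong acceptance and 99.97% power with the 2.5-year rates (3% v 0.5%), and 0.02% and 86.4% with the 7.5-year rates (6% v 1.5%). At none of the three landmarks does it meet both stated figures.

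**The case against.** A reader might infer that the other 540 - 386 = 154 patients (29%) enter no decision. The document does not support that. The 154 match the attrition allowance added to 386, the text speaks of two efficacy stages, and the sample size rests on cited methods for single-arm designs. So 386 may well be the final stage and the interim heading merely loose. The rate-based stopping rule and the 95% interval are also not restricted to the first 386 patients.

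A reader might also infer that using everyone enrolled would restore both alpha and power. That holds reliably only from about 430 evaluable patients, a total loss of about 20% (430 / 540 = 79.6%). Under the plan's own losses, alpha can be held but power cannot reach 95%.

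Two further points stand. The 2.7% at 386 arises because a limit of 8 is too lenient for that number, not because patients are left unused. And adapting a limit to the number actually evaluable is often left to an analysis plan, which is not shown here.

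These points do not remove the problem. The article itself fixes the number and the limit, counts treated patients, and states an alpha that the pair does not meet at 5 years. The rate rule is a point-estimate rule and the interval has no stated decision threshold, so neither serves as an acceptance rule at alpha 0.01.

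**Conclusion.** The point holds in a limited form. The last count-based decision is tied to a limit of 8 at 386 treated patients, is called interim, and has no counterpart for the number actually evaluable. At the 5-year pair, wrong acceptance is 2.7% at 386, and 6.1% to 9.2% at the 346 to 324 patients that the planned losses would leave, against a stated 1%. This rests on one-sided alpha, the 5-year rates, complete status for those counted, and the look at 144 being applied as printed. That 386 was meant as the evaluable number is plausible but inferred. The change is worth making before the final analysis, because the printed rule misses a stated design figure.

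**What to change.** - Say which analysis is final, name its landmark, and base it on all patients evaluable at that landmark.
- Set its limit as the largest relapse count whose exact acceptance probability at the minimum level, given the earlier looks, is at most 0.01 for the number actually evaluable. With the look at 144 at 5 years this is 5 of 324 or 346, 6 of 386, 8 of 432 and 11 of 540.
- If 386 is kept as a look that can only reject, state its limit and include it in the calculation. With >8 kept there and 11 of 540 at the end, alpha is 0.6% and power 97.8%. Using 6 as the limit at 386 would hold power to at most 90.4%.
- Restate the power for the evaluable number, and do not promise 95% under the planned 20% + 20% loss.

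The cost is wording and one exact calculation. The verdict comes later: at even accrual over 60 months (540 / 60 = 9 a month), patient 386 enters at month 42.9 and patient 540 at month 60, a difference of about 17 months, which lies within the planned 10-year follow-up.

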**Methods/Design:**

This prospective, multicentric single arm phase II study is based on the protocol of the international TARGIT-A study. The TARGIT-E study should confirm the efficacy of a single dose of intraoperative radiotherapy (IORT) in a well selected group of elderly patients with small breast cancer and absence of risk factors. Patients will receive IORT (20 Gy with Intrabeam system/Carl Zeiss) during breast conserving surgery. In presence of risk factors postoperative WBRT will be added to complete the radiotherapeutic treatment according to international guidelines. Endpoints are the local relapse rate (within 2 cm of the tumor bed), ipsilateral in breast relapse, cancer-specific and overall survival and contralateral breast cancer as well as documentation of quality of life and cosmetic outcome.

The expected local relapse rates are 0.5/1/1.5% after 2.5/5/7.5 years, respectively. Discontinuation of the trial is scheduled if rates of local relapse rates rise to 3/4/6% after 2.5/5/7.5 years. Power calculations result in 540 patients with a calculated dropout rate of 20% and loss to follow-up of 20%, an alpha of 0.01 and a beta 0.05. There will be a pre- and a post-pathology stratum (n = 270 each).

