#### Investigator withdrawal

The steering committee is allowed to close the study ahead of schedule.

Other stop-criteria might be:

Insufficient recruitment

Unexpected high toxicity

Any grade V toxicity

More than 3 grade IV toxicities within the first 20 patients

More than 5 grade IV toxicities within the first 50 patients

Ethical and medical considerations with regard to new evidence (benefit/risk ratio).

More than 5 local relapses after the first safety report

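### The stopping limits given as rates (3/4/6%) and as relapse counts (more than 5, more than 8) disagree on the same data, and the counts do not deliver the stated alpha and power

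*Protocol article*

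**What the plan says.** All references are to the protocol article.

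- **Planned interim analysis** sets two looks: "The first after 144 patients and the second after 386 patients were treated". It gives the expectation, "The expected local recurrence rate is 0.5/1/1.5% after 2.5/5/7.5 years, respectively", then the limit in rate form, "Stopping rules for the study are if the local recurrence rate is higher than 3/4/6% after 2.5/5/7.5 years", and directly after it the limit in count form: "Therefore the efficacy of IORT will be rejected if more than 5 or > 8 patients show a local relapse, respectively".
- **Abstract, Methods/Design** gives only the rate form: "Discontinuation of the trial is scheduled if rates of local relapse rates rise to 3/4/6% after 2.5/5/7.5 years".
- **Description of the primary efficacy analysis and population** lists the complements of the same rates (97/96/94% relapse-free) as the lowest acceptable level and 99.5/99/98.5% as the anticipated level.
- **Study hypothesis** sets alpha 0.01 and power 95%, names the A'Hern, Simon and Fleming designs, and arrives at 540 patients.
- **Investigator withdrawal**, in a list that opens "Other stop-criteria might be", includes "More than 5 local relapses after the first safety report".

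The article does not say which form takes precedence.

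**The concern.** The counts are presented as a consequence of the rates. If the rates are limits on what is observed, each count should be the smallest number of relapses that exceeds the matching rate at that look. It is not, except in one case. Three rates at three landmarks are also paired with two counts, and the looks are defined by patients treated, so the text does not show which rate belongs to which count.

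This boundary decides whether a single-arm trial continues and whether IORT is judged effective. If two stated limits give opposite answers and neither has precedence, the choice between them can be made after the relapses are known.

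**Working it through.** **Inputs.** Looks at 144 and 386; count limits >5 and >8; rate limits 3/4/6% and expected rates 0.5/1/1.5% at 2.5/5/7.5 years (Planned interim analysis); alpha 0.01, power 0.95, 20% drop-out, 20% loss to follow-up, N = 540 (Study hypothesis). Assumptions: alpha is one-sided, and rates are crude proportions of 144 and 386 with complete follow-up.

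**1. The plan's own sample size.** 386 × (1 + 0.20 + 0.20) = 540.4, which matches 540. Exact single-stage (A'Hern) designs at alpha 0.01 and power 0.95, with the largest acceptable number of relapses, are:

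- 3% vs 0.5%: n = 383, at most 4
- 4% vs 1%: n = 396, at most 7
- 6% vs 1.5%: n = 263, at most 7

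The first two sizes are close to 386. None of the three accepts 8 relapses.

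**2. Rates turned into counts.** The smallest count above the limit is the first integer above n × rate.

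| Look | 3% (2.5 y) | 4% (5 y) | 6% (7.5 y) | Count rule |
|---|---|---|---|---|
| 144 | 4.32 → 5 | 5.76 → 6 | 8.64 → 9 | 6 |
| 386 | 11.58 → 12 | 15.44 → 16 | 23.16 → 24 | 9 |

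Only one cell agrees with the count rule: 4% at the first look. No product is a whole number, so the abstract's slightly different wording (reaching rather than exceeding the rate) changes nothing here.

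**3. Where the two forms conflict.**

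- First look: 5/144 = 3.47%. This is above 3%, but not more than 5.
- Second look: 9/386 = 2.33% to 11/386 = 2.85%. This is more than 8, but below all three rates, so no choice of landmark removes the conflict. Against the 5-year limit of 4% the conflict covers 9 to 15 relapses (15/386 = 3.89%).

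Exact binomial probabilities of landing there:

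| True rate | 5 of 144 | 9–11 of 386 | 9–15 of 386 |
|---|---|---|---|
| 1% | 0.012 | 0.016 | 0.017 |
| 1.5% | 0.045 | 0.115 | 0.130 |
| 2% | 0.093 | 0.277 | 0.363 |
| 3% | 0.169 | 0.329 | 0.696 |

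**4. If 3/4/6% are null rates and the counts are the boundary.** The trial accepts IORT if X₁ ≤ 5 in 144 and X₁ + X₂ ≤ 8 in 386, where X₂ comes from the next 386 − 144 = 242 patients:

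P(accept | p) = Σ (x = 0 to 5) P(X₁ = x; 144, p) × P(X₂ ≤ 8 − x; 242, p)

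| Landmark | Alpha (null rate) | Power (expected rate) |
|---|---|---|
| 2.5 y | 0.177 (3%) | 0.9997 (0.5%) |
| 5 y | 0.027 (4%) | 0.981 (1%) |
| 7.5 y | 0.0002 (6%) | 0.864 (1.5%) |

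The first two miss alpha 0.01 and the third misses power 0.95. A different count at 386 would not repair the 5-year pair: in a single look, at most 7 relapses gives alpha 0.0126 and power 0.958, and at most 6 gives 0.005 and 0.904.

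**5. The bullet under Investigator withdrawal.** If it refers to the first look, it is the same as more than 5 of 144. If it is cumulative beyond that look, 6 to 8 relapses in 386 (1.55% to 2.07%) meet it while staying within the limit of 8.

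**The case against.** The best defence is that 3/4/6% were never meant as cut-offs for the observed rate. The section on the primary efficacy analysis treats their complements as the minimum acceptable level, and the named designs always put the rejection count well below n times the null rate. On that view 9 of 386 against a 4% null is ordinary, and the step from rates to counts is the usual one from null value to boundary. This reading is plausible, and if adopted it removes the formal conflict. It does not rescue the text: the abstract and the interim-analysis section both word the rates as grounds for stopping, and the counts miss the stated errors at every landmark.

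Several other objections stand in part:

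- The second-look conflict is rare (0.016) at the expected 5-year rate of 1%. It becomes common only if relapse exceeds expectation, which is when the rule is needed.
- At the second look the count is stricter than every rate, so following the count errs towards rejecting IORT.
- Kaplan-Meier plots are planned under Study objectives, and Kaplan-Meier rates would shift the exact counts.
- An article condenses a fuller protocol. The point here is not absent detail, though, but two printed limits that disagree.

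Two stronger readings are tempting. A reader might treat staying below a rate limit at 386 patients as a formal pass and work out its error rate. No section calls that a pass, and the only explicit rejection criterion is the count. A reader might also infer that the Investigator withdrawal bullet is a third contradictory rule that would halt a trial performing as planned. The list is permissive, and the number equals the first-look count. On that reading the chance of more than 5 in 144 is 0.003 at 1% and 0.022 at 1.5%.

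**Conclusion.** The concern holds for the rate and count limits. As crude proportions they give opposite answers at 5 of 144 (2.5-year limit only) and at 9 to 11 of 386 (every limit), widening to 9 to 15 against the 5-year limit. Reading the rates as null values exchanges the contradiction for a calibration error: alpha is 0.177 or 0.027 instead of 0.01 at 2.5 and 5 years, and power is 0.864 instead of 0.95 at 7.5 years. The text is therefore wrong on either reading. The Investigator withdrawal bullet is ambiguous, not clearly contradictory: it probably restates the first-look count and conflicts with the limit of 8 only if read cumulatively.

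The figures rest on crude proportions, complete follow-up of 144 and 386 patients, and a one-sided alpha.

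**What to change.** Reconcile the abstract, Planned interim analysis and Investigator withdrawal into one statement that:

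1. says whether 3/4/6% are null rates or cut-offs for the observed rate;
2. ties each count to one look and one landmark;
3. makes the relapse bullet under Investigator withdrawal refer to that rule;
4. reports the alpha and power that the chosen counts actually give, in place of 0.01 and 95%.

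Item 4 is needed because re-deriving the second-look count from alpha 0.01 cannot also keep 95% power at 386 patients for 4% against 1%. The cost is a short wording amendment and less favourable stated error rates. No extra patients are needed.

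### One pair of relapse limits (>5 of 144, >8 of 386) serves three hypothesis pairs with no landmark or null named, and gives alpha 0.01 with 95% power at none of them

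*Protocol article*

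**What the plan says.** All references are to the protocol article.

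- **Study hypothesis** states the error rates once: "Power calculations with an alpha set at 0.01, a beta set at 0.05 (power 95"%). It gives neither the landmark nor the null hypothesis. It names three phase II design methods, including an exact single-stage method and Fleming's multi-stage method, and describes the aim as confirming non-inferiority to WBRT.
- **Description of the primary efficacy analysis and population** gives three hypothesis pairs. The expected level is: "A response rate of 99.5%/99%/98.5% at 2.5/5/7.5 years is anticipated". The lower bar is: "A response rate of 97%/96%/94% is considered to be the minimum level". In relapse terms these are 0.5% v 3%, 1% v 4% and 1.5% v 6%. Two analysis stages are planned.
- **Planned interim analysis** places the looks at 144 and 386 treated patients, repeats the three expected and three stopping rates, and concludes: "Therefore the efficacy of IORT will be rejected if more than 5 or > 8 patients show a local relapse, respectively".
- **Investigator withdrawal** lists more than 5 local relapses after the first safety report among the possible stopping criteria. This fits reading 5 as the limit at the first look and 8 as the cumulative limit at the second.

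**The concern.** One pair of counts cannot have the same error rates for three hypothesis pairs that differ this much. With 386 patients the expected number of relapses under the acceptable rates is 386 × 0.005 = 1.9, 386 × 0.01 = 3.9 and 386 × 0.015 = 5.8. Under the unacceptable rates it is 11.6, 15.4 and 23.2. A limit of 8 is therefore loose at 2.5 years and tight at 7.5 years.

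This is the only numerical decision rule for the primary endpoint of a single-arm trial in which patients without risk factors receive IORT and no WBRT. If the landmark and the null are left open, they can be chosen after the relapse counts are known, and the printed alpha and power do not describe the rule that will be applied.

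**Working it through.** **Inputs.** Looks at n1 = 144 and n = 386 (242 further patients); limits 5 and 8; relapse rates 0.5/1/1.5% expected and 3/4/6% unacceptable; alpha 0.01; power 0.95. Every patient is taken as evaluable at the landmark.

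**Reproducing the plan's figures.** 386 × 1.40 = 540.4, so the total of 540 agrees with 386 inflated by the two 20% allowances added together.

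The limits themselves can be reproduced with Fleming's normal-approximation boundary, n_k·p0 + z·√(N·p0·(1−p0)), taking p0 = 1% (the 5-year expected rate), N = 386 and z = 2.326 (one-sided alpha 0.01):
- √(386 × 0.01 × 0.99) = 1.955, and 2.326 × 1.955 = 4.55
- first look: 1.44 + 4.55 = 5.99, so reject at 6 or more, i.e. >5
- second look: 3.86 + 4.55 = 8.41, so reject at 9 or more, i.e. >8

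The same formula gives 3.94 and 5.15 at 2.5 years (reject at ≥4 and ≥6), and 7.72 and 11.35 at 7.5 years (≥8 and ≥12). On this formula the printed limits match the 5-year pair only.

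**Exact error rates of the printed rule.** IORT is accepted if there are at most 5 relapses in the first 144 patients and at most 8 in all 386:

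P(accept | p) = Σ (x = 0 to 5) Bin(x; 144, p) × P[Bin(242, p) ≤ 8 − x]

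| Landmark | Pair | P(accept at unacceptable rate) | P(accept at expected rate) |
|---|---|---|---|
| 2.5 y | 0.5% v 3% | 0.177 | 0.9997 |
| 5 y | 1% v 4% | 0.0268 | 0.981 |
| 7.5 y | 1.5% v 6% | 0.0002 | 0.864 |

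Ignoring the first look changes little: 8 of 386 as a single-stage rule gives 0.180/0.9998, 0.0274/0.983 and 0.0002/0.870.

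**Reading A: alpha is the risk of accepting IORT at the minimum level.** Alpha/power are the two table columns: 0.177/0.9997, 0.027/0.981, 0.0002/0.864. Alpha fails at 2.5 and 5 years; power fails at 7.5 years.

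**Reading B: alpha is the risk of rejecting IORT at the expected rate.** Alpha is 1 minus the last column and power is 1 minus the column before it: 0.0003/0.823, 0.0187/0.973, 0.136/0.9998. Power fails at 2.5 years; alpha fails at 5 and 7.5 years.

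**Can another final limit at 386 meet both targets at 5 years?** With >5 of 144 kept at the first look:

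| Final limit | P(accept at 4%) | P(accept at 1%) | P(reject at 1%) | P(reject at 4%) |
|---|---|---|---|---|
| >6 | 0.0051 | 0.904 | 0.096 | 0.995 |
| >7 | 0.0125 | 0.957 | 0.043 | 0.988 |
| >8 | 0.0268 | 0.981 | 0.019 | 0.973 |
| >9 | 0.0509 | 0.991 | 0.0087 | 0.949 |

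On Reading A no row meets both: >6 falls short on power and >7 exceeds alpha. With the first look kept, the smallest final number that works is 396 with limit >7 (0.0098/0.951). On Reading B, >9 meets alpha and misses 95% power by 0.001.

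**The case against.** The strongest defence is that the rule is written as a test that rejects IORT when relapses are too many, that Fleming is among the named methods, and that Fleming's boundaries with a 1% null at alpha 0.01 give exactly these counts. Alpha is then the risk of wrongly rejecting IORT, and 0.027 at 5 years is a beta comfortably inside 0.05. This defence stands in part. It identifies the likely landmark, and it means the documents do not support stating as fact that the 5-year alpha is 0.027, or that ineffective IORT is accepted nearly three times as often as claimed. It does not rescue the printed figure: on that reading the exact alpha is 0.019, because the normal approximation is poor with about four expected events. Reading A also remains the better fit to a stated minimum level and a non-inferiority aim.

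Second, alpha and power are stated once, not for each landmark. A reader might infer from the 2.5- and 7.5-year results that the plan contains three separate arithmetic errors, such as an 18-fold alpha at 2.5 years. The text does not go that far. Those values show what happens if the counts are used at those landmarks, which the wording leaves open.

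Third, a reader might see a contradiction in the planned estimate of the "true response rate with a 95% confidence interval": at 8 of 386 the exact upper limit is 4.04%, just above 4%. That interval is given for estimation while the decision is made by counts, so a mismatch with alpha is a matter of preference and no error.

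**Conclusion.** The point holds as a failure to meet alpha and power jointly, combined with an unnamed landmark and null hypothesis. On neither reading of alpha do the printed limits give alpha at or below 0.01 together with power of at least 95% at any landmark. At 5 years the gap is moderate: the two exact errors are 0.027 and 0.019, both below 3%, against a stated 0.01 for whichever of them is alpha, and power is above target on both readings. Used at 2.5 or 7.5 years, the same counts perform far from the stated rates (0.177 risk of accepting 3%; 0.136 risk of rejecting at 1.5%).

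A reader might go further and conclude that the 5-year limit is too lenient and must come down. The documents do not support this. With a 4% null the limit would fall to >7 or >6; with a 1% null it would rise to >9. The direction cannot be settled until the null is stated.

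The calculation assumes that 386 is the cumulative number at the second look, that the limits are cumulative, and that all patients are evaluable at the landmark. With fewer evaluable patients under the same limits, the risk of accepting a 4% rate rises; for example it is 0.061 at 540 × 0.8 × 0.8 ≈ 346.

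**What to change.** 1. State the landmark and the null hypothesis to which the limits apply, and which error is alpha. Five years, 1% v 4%, is the pair the limits reproduce. State that these counts are not used at 2.5 or 7.5 years.
2. Then do one of the following:
   - keep >5 of 144 and >8 of 386 and replace the stated error rates with the exact 5-year ones: 2.7% risk of accepting a 4% relapse rate and 1.9% risk of rejecting at 1%; or
   - reset the final limit and print its exact two-look rates. With a 4% null, >7 of 386 gives alpha 0.0125 and power 0.957, and >6 gives 0.005 and 0.904. With a 1% null, >9 gives alpha 0.0087 and power 0.949.
3. If limits are wanted at the other landmarks, give each its own, with two-look error rates. With the null at the unacceptable rate and >5 of 144 kept, >4 of 386 at 2.5 years gives 0.009/0.954, and >12 of 386 at 7.5 years gives 0.0055/0.974.

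The cost is wording and slightly less favourable stated error rates. No change to the sample size is needed. Aligning the confidence level of the reported interval with alpha is optional.
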